#### USUAL CARE

Before the introduction of structured survivorship care in BETER clinics, follow-up of lymphoma survivors was usually discontinued 5 years after lymphoma treatment (wait-and-see policy with regard to late adverse lymphoma treatment effects). In usual care this means that late effects like thyroid dysfunction, breast cancer, cardiovascular disease and increased risk of infections are usually not diagnosed until patients present with severe symptoms. In addition, a significant doctors' delay may occur since survivors generally present with these diseases at younger ages than the general population, often <50 years. Consequences of delays in diagnosis may include more advanced stage of disease leading to more intensive treatment, higher morbidity and mortality and increased health care costs.

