### 1.6 OUTCOME (O)

#### 1.6.1 Primary

- 1) (Cost-)effectiveness of structured survivorship care at the BETER clinics in terms of:
  - a. Burden of disease in disability adjusted life years (DALYs) from CVD (including risk factors for CVD), breast cancer, hypothyroidism and functional asplenia
  - b. Health care costs related to CVD (including risk factors for CVD), breast cancer, hypothyroidism and functional asplenia
  - c. Health-related quality of life (HRQoL) and QALY's using the 36-item Short Form Health Survey (SF-36) and the 5 dimension/5-level EuroQoL (EQ-5D-5L) questionnaire
  - d. Health-related productivity losses using the iMTA Productivity Cost Questionnaire (iPCQ).
- 2) The yield of previously undiagnosed adverse events from screening and the incidence of adverse events during follow-up
  - a. At prevalent and incident screening of survivors attending the BETER clinic (for those survivors in the intervention group who are attending the BETER clinic)
  - b. From hospital records, Netherlands Cancer Registry, The National Heart Registry, GP records, Dutch Hospital Data registry, and BETER questionnaire: for all included survivors, to allow valid comparison between the intervention and comparison groups

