##### 1.6.1.1. Assessment of Yield of Screening and Incidence of Adverse Events

For the primary outcomes, we will first determine the yield of previously undiagnosed adverse events during follow-up, i.e. between 2013-2016 and 2021-2024. This information will be extracted from hospital medical records, the survivors' general practitioners, disease registries and the self-administered BETER questionnaire.

Before their clinic visit survivors are asked to complete a questionnaire on their current health, medical history, and lifestyle. This so-called BETER questionnaire helps healthcare providers to focus on actual symptoms of late effects and on lifestyle during the consultation. The questionnaire contains items on general background (e.g. marital status, level of education), medical history (adverse events, including reproductive history and fatigue), family history, medication, screening history, physical activity, weight, alcohol, smoking and recreational drug use, as well as psychosocial problems, difficulties with employment, insurance coverage, and mortgages. The BETER questionnaire will also be mailed to eligible survivors who decided not to visit a BETER clinic. In line with the intervention group, the survivors in the control group will fill in the BETER questionnaire at their first BETER visit in 2021-2024 or through mail (for non-responders). The BETER questionnaire thus provides the proposed project with important information on existing morbidity/diseases prior to the first BETER visit and on characteristics of the BETER visitors. The response to The BETER questionnaire is very high, ranging between 90-95%.

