For the intervention group trained data managers will access the BETER medical records in the BETER clinics and collect the relevant data from all BETER visits, including all screening/diagnostic tests during follow-up and their results. For all survivors included in the study (intervention and comparison groups) we will obtain information on the incidence of clinical events of interest through linkage with disease registries. Information on second malignancies will be obtained from The Netherlands Cancer Registry, information on cardiac interventions will be obtained from The National Heart Registry, information on hospital admissions for CVD and serious infections (overwhelming post-splenectomy infections) will be obtained from Dutch Hospital Data and cause of death for those who died during follow-up will be obtained from Statistics Netherlands. We will also approach the general practitioners of all patients to obtain data on CVDs (especially those not requiring hospital admission, such as angina pectoris), cardiovascular risk factors (hypertension and hypercholesterolemia) and hypothyroidism.

Survivors' informed consent for the above data collection is asked at the first visit to a BETER clinic. For included survivors who choose not to visit a BETER clinic informed consent for linkage with disease registries and approach of general practitioner is requested by mail. Currently over 97% of all patients visiting a BETER clinic has provided consent. Informed consent for the control group will be obtained during the patients' first visit at a BETER clinic in 2021-2024 and is not necessary for deceased individuals.

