##### 1.6.1.2. Assessment of Burden of Disease

In the proposed study, burden of disease from morbidity and mortality from CVD (including risk factors), breast cancer,

hypothyroidism and overwhelming post splenectomy infections due to functional asplenia is measured in 'disability adjusted life-years' (DALYs). One DALY can be thought of as one lost year of "healthy" life. DALYs for a disease or health condition are calculated as the sum of the 'years of life lost' (YLL) due to premature mortality and the 'years lost due to disability' (YLD) for people living with the health condition or its consequences:  $DALY = YLL + YLD$ . The YLL correspond to the number of deaths multiplied by the standard life expectancy at the age at which death occurs. To estimate YLD for a particular health condition in a particular time period, the number of cases in that period is multiplied by the average duration of the disease (in years) and a weight factor (disability weight) that reflects the severity of the disease on a scale from 0 (perfect health) to 1 (dead). Disability weights are extracted from literature (18–21).

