### 1.7. SAMPLE SIZE CALCULATION

#### 1.7.1. Assessing the potential health gains

To assess the potential health gains (in terms of averted DALYs) of BETER survivorship care, a model was constructed in which the burden of disease accumulated during 5-year follow-up (note: the follow-up in the proposed study is expected to be longer) was calculated for the intervention group, screened at a BETER clinic, and the control group. The model includes cumulative incidence of the late adverse events after treatment under study: (risk factors of) CVD, breast cancer, hypothyroidism and overwhelming post-splenectomy infections due functional asplenia. The risk of these conditions is substantially increased: see 1.3.1. BETER Screening Recommendations for Late Adverse Effects after Lymphoma Treatment. The impact of treating the CVD risk factors high blood pressure and hypercholesterolemia on developing CVD and death from CVD was inferred from risk reduction tables published by the Dutch Society of General Practitioners ([www.nhg.org/sites/default/files/content/nhg\\_org/uploads/cvrm\\_protoc\\_bijlagen\\_web\\_13.pdf](http://www.nhg.org/sites/default/files/content/nhg_org/uploads/cvrm_protoc_bijlagen_web_13.pdf)). Disability weights for CVD were extracted from the Global and Dutch Burden of Disease studies (19,21). The number of DALYs averted by breast cancer screening was based on a cost-effectiveness study on breast cancer interventions (28). Based on this model, we estimated that the average HL survivor of 52 years of age, who is not screened for late adverse treatment events, acquires 1.18 DALYs in the next 5 years (1.12 for breast cancer + CVD; 0.01 for hypothyroidism; 0.04 for functional asplenia), as opposed to 0.56 DALYs for a survivor screened at a BETER clinic (0.55 for breast cancer + CVD; 0.00 for hypothyroidism; 0.00 for functional asplenia). [Of note, the numbers do not add up due to rounding.] We therefore assume that, at patient level, screening at the BETER clinics averts on average 0.62 DALYs per survivor in a 5-year period. In the 1.8. DATA-ANALYSIS section we describe that we will perform an 'intention to screen' analysis, assessing the impact of BETER survivorship care including survivors who choose not to attend. Preliminary data from a small study in a few BETER clinics showed an attendance rate of 60-70%. When we take an attendance rate of 65% into account, the expected difference between the intervention and the control group is 0.40 DALY: 0.78 DALYs in the intervention group (65% of 0.56 DALYs + 35% of 1.18 DALYs) and 1.18 DALYs in the control group.

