#### 1.8.2. Patient level analysis

To assess the impact of BETER survivorship care on screened/treated individuals, outcome parameters will be compared between the first 270 survivors who attended a BETER clinic that started in 2013-2014 and matched survivors who are not (yet) screened and were treated for lymphoma at BETER centres that start a clinic in 2021-2024.

On both levels of analysis, multiple linear regression analysis will be used for continuous outcomes (such as DALYs and health care costs) and Poisson or negative binomial regression analysis will be used for count variables (i.e. yield of previously undiagnosed adverse events). The regression analyses will also take the amount of follow-up time into account, thereby correcting for a possible difference in follow-up time in the intervention and control group.

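### Comparing screening yield between the arms by count regression measures detection as well as disease, and can show an excess of late effects under BETER care with no true effect

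*Protocol*

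**What the plan says.** Section 1.6.1 lists, as the second primary outcome, the yield of screening and the incidence of adverse events. It has two parts. Part 2a is yield at screening, in intervention survivors who attend the clinic. Part 2b uses hospital, registry, GP and questionnaire data "for all included survivors, to allow valid comparison between the intervention and comparison groups".

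Section 1.6.1.1 does not keep the parts separate: "we will first determine the yield of previously undiagnosed adverse events during follow-up, i.e. between 2013-2016 and 2021-2024". Section 1.8.2 then fixes the analysis for both levels: "Poisson or negative binomial regression analysis will be used for count variables (i.e. yield of previously undiagnosed adverse events").

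On detection:
- The Usual Care section says that late effects in unscreened survivors "are usually not diagnosed until patients present with severe symptoms".
- Section 1.3.1 gives attenders risk-based cardiovascular, breast and thyroid testing.
- For the intervention arm, section 1.6.1.1 has data managers "collect the relevant data from all BETER visits, including all screening/diagnostic tests during follow-up and their results".
- Under section 1.5, a control's follow-up ends at the first BETER visit, which is normally the first systematic screen.

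On DALYs, section 1.6.1 defines the outcome as "Burden of disease in disability adjusted life years (DALYs) from CVD (including risk factors for CVD), breast cancer, hypothyroidism and functional asplenia". Section 1.6.1.2 computes YLD by a rule in which "the number of cases in that period is multiplied by the average duration of the disease (in years) and a weight factor (disability weight") reflecting severity.

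**The concern.** Yield is a measure of detection. The hypothesis is that BETER care reduces the burden of late effects. If one arm is tested systematically for years and the other is tested mainly when symptoms appear, the tested arm will record more diagnoses even if the underlying disease is identical. Part of a primary outcome would then move against the intervention because the screening works as intended.

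The wording of 2b suggests that common data sources make the comparison valid, but common sources do not give common detection. Section 1.6.2.1 refers to referral of survivors to their GP for cardiovascular risk management. Section 1.6.1.1 then relies on GP records for hypertension, hypercholesterolaemia and hypothyroidism, three conditions whose diagnosis depends heavily on testing. Matching, the instrumental variable and the adjustment for follow-up time do not address who gets tested.

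The YLD rule raises a related question. If a silent case found by screening counts from the date of detection with a positive weight, it adds burden that the same silent case in a control does not add.

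**Working it through.** **The plan's own figures.** Section 1.7.1 gives 0.56 DALYs for a screened survivor, 1.18 for an unscreened one, and 65% attendance. Intervention arm: 0.65 × 0.56 + 0.35 × 1.18 = 0.777, stated as 0.78. Difference: 1.18 − 0.777 = 0.403, stated as 0.40. Both reproduce, and this point does not turn on them.

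**Counts with no true effect.** Let d be the share of true cases that usual care diagnoses within follow-up (assumed), and let attenders have 95% of cases diagnosed (assumed). Attendance of 65% is from the protocol.

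Intention to screen: rate ratio = (0.65 × 0.95 + 0.35 × d) / d
- d = 0.8: 0.8975 / 0.8 = 1.12
- d = 0.6: 0.8275 / 0.6 = 1.38
- d = 0.5: 0.7925 / 0.5 = 1.585

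Patient level, attenders against unscreened controls: rate ratio = 0.95 / d
- d = 0.8: 1.19
- d = 0.5: 1.90

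Section 1.8.1 allows for up to 5% uptake among controls. At 5% the denominator becomes 0.05 × 0.95 + 0.95 × d:
- d = 0.8: 0.8975 / 0.8075 = 1.11
- d = 0.5: 0.7925 / 0.5225 = 1.52

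**A check from the documents' only lead time.** The efficiency-gain appendix costs thyroid medication over 33 years under BETER and 31.5 years under usual care, a lead of 1.5 years. Assume steady incidence, every case eventually diagnosed, and the expected 8 years of follow-up. The rate ratio is then 1 + 0.65 × 1.5 / 8 = 1.12. A ratio of 1.585 would need a lead of 0.585 × 8 / 0.65 = 7.2 years.

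**Chance of a significant apparent harm.** Assume 393 per arm, Poisson counts, 0.2 to 0.4 true events per person, and full detection in attenders, so that the ratio is (0.65 + 0.35 × d) / d. At d = 0.8 (ratio 1.16) the chance is 14% to 24%. At d = 0.5 (ratio 1.65) it is 70% to 94%.

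**DALYs.** Let p be the share of attenders with a silent condition found only by screening, and w its disability weight (both assumed). Count over 5 years, the horizon of the planned 0.40. Spurious YLD per invited survivor = 0.65 × p × w × 5
- p = 0.10, w = 0.01: 0.00325, or 0.8% of 0.40
- p = 0.30, w = 0.05: 0.04875, or 12% of 0.40
- w = 0: zero

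**The case against.** The strongest reply is that the protocol already separates yield in attenders from incidence in common sources, that section 2.1 expects screening to find disease earlier, and that a higher yield therefore need not be read as harm. The separation in section 1.6.1 is real and is the right starting point. It does not survive into section 1.8.2, which names yield itself as the regression outcome at both levels.

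The size is uncertain, and this stands. One detection rate for all conditions is a simplification: section 1.3.1 restricts breast imaging, thyroid testing and echocardiography to treatment subgroups, and asplenia has no screening test. The only lead time in the documents points to the lower end of the range.

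A reader might infer that screening happens in one arm only. That is too firm. Up to 5% of controls may attend, sections 1.6.2 and 1.6.2.2 recognise screening elsewhere, and sections 1.5 and 1.6.1.1 leave it unclear whether findings at the controls' closing visit count. If they do, the count bias shrinks.

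A reader might also infer that the DALY benefit is necessarily understated, and that the YLD rule contradicts the planning model, in which a screened survivor has "0.00 for hypothyroidism; 0.00 for functional asplenia". The documents do not support this. The weights reflect severity, section 2.3 also refers to severity, and nothing assigns silent screen-detected disease a positive weight or a start date at detection. If early-treated disease carries little or no weight, the planned fall from 0.01 to 0.00 for hypothyroidism is consistent with the rule. YLL is not affected by lead time. Nor should the bias be put near 20% by accruing YLD over 8 years (0.65 × 0.30 × 0.05 × 8 = 0.078): the 0.40 is a 5-year difference, so the periods do not match.

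**Conclusion.** The count comparison as written is biased by detection and should be changed. Its direction follows from the protocol's own account of usual care and of the screening programme. With no true effect, the apparent rate ratio at intention-to-screen level is about 1.12 to 1.58 for usual-care detection of 80% to 50%. Those detection rates and the 95% in attenders are assumptions and would differ by condition.

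For DALYs the conclusion is conditional. The benefit may be understated if asymptomatic screen-detected disease carries a positive weight from the date of detection: about 1% to 12% of the planned 0.40 under the assumptions shown, and nothing if the weight is zero. The statistical analysis plan is not available here and may settle the weights. It would still have to depart from the outcome that section 1.8.2 names.

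**What to change.** 1. In sections 1.6.1 and 1.8.2, report yield descriptively in intervention attenders only, as part 2a already implies, and remove it from the between-arm regression.
2. Base the between-arm count comparison on clinically manifest events already linked for both arms: admissions for CVD and serious infection, cardiac interventions, and cause-specific death. These depend less on screening, though cardiac interventions are not wholly free of it.
3. Report breast cancer separately, because its diagnosis remains sensitive to screening. Show it by stage where available; section 1.6.1.1 does not list stage among the linked data.
4. Keep all-diagnoses incidence as a secondary analysis, labelled as subject to detection bias.
5. State whether findings at the controls' first BETER visit count.
6. In section 1.6.1.2, use severity-specific weights and state the onset date for screen-detected disease. Add a sensitivity analysis that gives asymptomatic screen-detected conditions no YLD. CVD risk factors can stay in the primary DALY as declared.

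The cost is mainly protocol and analysis wording. Stage may need an additional registry item if it is not already supplied. The statistical price is fewer countable events and so a less precise count comparison.

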### 1.5 FOLLOW-TIME (T)

To facilitate follow-up of at least 5 years at the BETER clinics, the follow-up of lymphoma survivors in the intervention group starts in 2013-2016, when they were first invited to attend the BETER clinic, and ends in 2021-2024 at their most recent BETER visit. The start of follow-up of survivors in the control group will correspond to that of the intervention group and ends at their first BETER visit in 2021-2024. The follow-up of survivors who do not attend the BETER clinic (i.e. non-attenders in both the intervention and control groups) ends on completion of the mailed questionnaires. Furthermore, if survivors either in the intervention group or comparison group die during follow-up, follow-up ends at death. Expected median follow-up time is 8 years.

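### The DALY regression corrects for follow-up time that death itself shortens, so the correction does not repair a follow-up difference between the groups and usually worsens it

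*Protocol*

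**What the plan says.** Section 1.8.2 sets the model for both the intention-to-screen and the patient-level analysis: "multiple linear regression analysis will be used for continuous outcomes (such as DALYs and health care costs"). The next sentence adds the correction: "The regression analyses will also take the amount of follow-up time into account, thereby correcting for a possible difference in follow-up time". It does not say whether time enters as a covariate, an offset or the denominator of a rate.

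Section 1.5 defines the time in question.
- For attenders in the intervention group, follow-up "ends in 2021-2024 at their most recent BETER visit".
- For attenders in the control group it "ends at their first BETER visit in 2021-2024".
- For non-attenders in either group it "ends on completion of the mailed questionnaires".
- For deaths: "if survivors either in the intervention group or comparison group die during follow-up, follow-up ends at death".

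The start of follow-up is aligned between the groups, and "Expected median follow-up time is 8 years".

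Section 1.6.1.2 defines DALY as YLL plus years lost due to disability (YLD). On the first part it says: "The YLL correspond to the number of deaths multiplied by the standard life expectancy at the age at which death occurs".

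**The concern.** These three rules work against each other. A person who dies two years after the index date has two years of follow-up and, at an assumed 30 years of remaining life expectancy, about 30 DALYs. A person alive at eight years has four times the follow-up and only the YLD. The shortest times therefore carry the largest outcomes, and they are short because of the outcome.

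The correction is meant to allow for more time at risk producing more DALYs, which needs a positive slope. A linear model given death-truncated time will tend to estimate a negative one. If one group is observed longer for administrative reasons, the model then moves the group difference the wrong way.

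DALYs are the first-listed primary outcome. The end-of-follow-up rules differ by group and attendance, and section 1.8.2 itself foresees a follow-up difference.

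**Working it through.** **The plan's own figures.** Section 1.7.1 expects 0.65 x 0.56 + 0.35 x 1.18 = 0.777 DALYs in the intervention group against 1.18 in the control group, a difference of 0.403 over 5 years (stated as 0.40). Section 1.7.2 gives 393 per group for 0.20 SD, and 393 x 1.15 = 452. Both figures reproduce.

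**True accrual.** 1.18/5 = 0.24 and 0.78/5 = 0.16 DALY per year, so about +0.2 per year. Carried to the expected 8 years, the planned effect is 0.40 x 8/5 = 0.64.

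**Algebra.** In a linear regression on group and observed time, this holds exactly:

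adjusted difference = unadjusted difference - slope x (difference in mean observed follow-up).

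With a positive slope, longer follow-up in one group is subtracted out. With a negative slope it is added on.

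**Simulation.** The protocol gives no YLL share, mortality rate or expected gap, so these are assumptions.
- One million subjects per group, calibrated to 1.18 and 0.78 DALYs per 5 years.
- Entry uniform over 2013-2016, end uniform over 2021-2024.
- 32 years of life lost for a death at the index date.
- Other-cause mortality 0.3% per year.
- YLL share 30%, 50% or 75%.

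| Quantity (DALY) | YLL 30% | YLL 50% | YLL 75% |
|---|---|---|---|
| No true effect, intervention group followed 0.5 year longer: adjusted for observed time | 0.33 | 0.50 | 0.69 |
| True effect about -0.6 over 8 years, intervention group followed 1 year longer: adjusted for observed time | -0.08 | +0.26 | +0.65 |

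In the first row the unadjusted difference is 0.11 and adjustment for potential follow-up gives 0.00-0.01. In the second row adjustment for potential follow-up gives -0.62 to -0.66.

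**Slope implied by the first row.** Solving the identity with a gap of 0.5 year gives (0.11 - 0.33)/0.5 = -0.44, (0.11 - 0.50)/0.5 = -0.78 and (0.11 - 0.69)/0.5 = -1.16. The observed gap is slightly under 0.5 because deaths shorten it, so the fitted slopes are a little steeper. The overall range is about -0.4 to -1.3. On potential follow-up the slope is +0.16 to +0.21.

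**Gap that yields a spurious 0.40.** Scaling the first row gives 0.40 x 0.5/0.33 = 0.61 year, 0.40 x 0.5/0.50 = 0.40 year and 0.40 x 0.5/0.69 = 0.29 year.

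**No gap.** With evenly spread dates, attenuation towards zero is about 0-11%. It grows when administrative dates are less spread. The largest value found was 39%, with an SD of 0.75 year, a YLL share of 80% and no other-cause deaths.

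**Low YLL share.** At 10% with widely spread dates the slope is near zero: -0.12 to -0.07 in one set of runs, and +0.01 to +0.06 in another with other-cause mortality of 0.5-1% per year. A 0.5-year gap then leaves a spurious 0.08-0.14.

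**Higher other-cause mortality.** Across 0-1% per year, the spurious difference at a 30% share and a 0.5-year gap is 0.23-0.39.

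**The case against.** Section 1.8.2 does not fix how time enters the model, and the same sentence covers the count models, where a time offset is standard. A pooled rate (total DALYs over total person-years) was nearly unbiased when tried. An analysis plan not shown here could settle this. That stands as a limit on the claim. It does not remove it, because a covariate is the ordinary meaning in a multiple linear regression. The other patient-level option, each subject's DALYs divided by own follow-up, is very unstable because early deaths give extreme values.

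A reader might infer that the correction always has the wrong sign. It does not: at a low YLL share the slope is near zero or slightly positive.

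A reader might also infer that an error of 0.40 is to be expected. The documents do not support that. It needs both a sizeable YLL share and a gap of some months in administrative follow-up. Section 1.5 aligns the start dates and gives both groups the same 2021-2024 end window. The end rules differ, but neither the size nor the direction of any gap is stated.

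Finally, the 5-year horizon is already used in the power calculation (1.7) and the cost-effectiveness analysis (2.1, 8.5.4). What is missing is its link to this regression.

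**Conclusion.** The point holds in conditional form. That follow-up ends at death and that death generates DALYs are both fixed by the protocol, so observed follow-up is an unsuitable adjustment variable for the linear DALY model whatever the numbers. As a covariate it does not correct a follow-up difference, and at assumed YLL shares of 30-75% it makes the difference worse.

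The size depends on assumptions the protocol cannot settle:
- **No administrative gap:** a modest loss of effect, about 0-11% with evenly spread dates.
- **Gap of about 0.5 year, YLL share 30-75%:** a spurious 0.3-0.7 DALY. This is comparable with the planned 5-year 0.40, and roughly half to all of its 8-year equivalent of 0.64.
- **Intervention group followed 1 year longer:** a true benefit can vanish or read as harm. A gap the other way would exaggerate it.

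Nothing in the protocol shows that such a gap will occur. The different end rules make it possible, and the stated correction would not protect against it.

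**What to change.** In section 1.8, define the DALY outcome for the regression as DALYs accumulated over a fixed 5 years from the matched index date, with no covariate for time truncated by death. This matches the horizon of the power calculation and the 5-year cost-effectiveness analysis.

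Use the registry and general-practitioner data described in 1.6.1.1 to complete the window where a clinic visit or questionnaire falls short of it. It should not be assumed that everyone reaches 5 years by their own end date: an index date in late 2016 and an end visit in early 2021 are just over 4 years apart. With uniform dates over two 4-year windows, the share below 5 years is 0.25 x 0.25/2 = about 3%. Treat these few as administratively censored, by a stated rule.

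For longer horizons, adjust only for potential follow-up, from the index date to an administrative date set independently of death. That date must also be defined for people who die, since they have no closing visit or questionnaire.

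The cost is a few sentences and no new type of data. The downside is that data after 5 years move to a secondary analysis.
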